### Hypothesis

It is feasible to conduct a randomized controlled trial in critically ill patients with hypoproteinemia to investigate the clinical effects of 25% albumin in addition to furosemide.

### Secondary objectives

For this pilot study, we will assess feasibility outcomes, but also collect physiologic and clinical outcome data, including volume of diuresis, oxygenation, duration of ventilation, length of ICU stay, and mortality. However, we expect the pilot study to be underpowered to demonstrate changes in these outcomes. If the pilot study successfully demonstrates feasibility, these unblinded data will be incorporated in the planned larger trial, in a nested fashion. We hypothesize that the use of intravenous 25% albumin in addition to furosemide, as opposed to furosemide alone, increases the volume of diuresis achieved, improves oxygenation, prevents intravascular volume depletion at 72 hours, and results in more ventilator-free days.

## Methods/Design

### Study design

The FADE study is a single-center, parallel, pilot randomized controlled trial. The primary outcome is feasibility, with secondary physiologic and patient-important outcome data also being collected.

### Participants

The target population is one of critically ill adults with hypoalbuminemia who are in a recovery phase of critical illness and judged by the treating physician to be volume overloaded, based on clinical findings, such as peripheral edema, delayed weaning, or chest radiographic findings of interstitial or pleural fluid. Thus, inclusion criteria include: (1) admission to ICU; (2) age ≥ 18 years; (3) hemodynamic stability for at least 24 hours, defined as the absence of persistent (>1 hour) hypotension (systolic blood pressure < 90 mmHg) and tachycardia (heart rate >110), not currently on vasopressors, received less than 2 l crystalloid or colloid boluses or two units of packed red blood cells, maintenance fluids excluded; (4) hypoproteinemia, defined as serum albumin < 30 g/l, or total protein < 60 g/l; (5) clinical decision by the caregiving team to diurese at least 3 l of net fluid balance within the next 72 hours, for any reason.

Patients will be excluded for any of the following reasons: (1) known pregnancy; (2) patient or surrogate decision maker unable or unwilling to consent to blood product administration, including albumin; (3) acute kidney injury (RIFLE criteria ‘F’ or greater with either tripling of creatinine or creatinine >355 μmol/l (with a rise of >44) or average urine output below 0.3 ml/kg/hour for 24 hours) without any improvement in the previous 24 hours, or otherwise expected to necessitate dialysis within 48 hours in the opinion of the treating physician; (4) chronic kidney injury requiring dialysis; (5) clinically documented cirrhosis; (6) clinically documented nephrotic syndrome; (7) serum sodium levels greater than 150 mEq/l or serum potassium levels less than 2.5 mEq/l that cannot be treated prior to administration of study treatment; (8) inability to measure urine output and fluid balance accurately; (9) receipt of hyperoncotic albumin within preceding 24 hours; (10) previous enrollment in this trial, or any other research studies for which co-enrollment is not permitted; (11) estimated survival or ICU stay less than 72 hours.

### Recruitment plans and consent process

The study will be carried out at two different ICUs within a single tertiary care academic center (Hamilton General Hospital and the Juravinski Hospital and Cancer Centre, Hamilton, Ontario, Canada). Both sites are research-intensive and serve a high volume of general medical and surgical critically ill patients. The recruitment process is outlined in Figure 
1 and Table 
4. Patients will be screened by study investigators within 72 hours of admission to the ICU. Patients present in the ICU for longer than 72 hours can be referred to study investigators by the team providing care if they believe that the patient might qualify for the study. Patients or surrogate decision makers will be approached by the research team and informed of the study rationale and methods, and provided with literature about the study. They will then be given an opportunity to consider study enrollment, in person or via phone. If the patient is willing, consent for the research study as well as blood product administration, if it has not already been received by the caregiving team, will be obtained. Patients will be screened and randomized once the caregiving team decides diuresis is necessary, but prior to administering diuretics from the caregiving team.

**Figure 1 F1:**
[figure not shown]
**Patient recruitment and randomization process.** ICU, intensive care unit; IV, intravenously, SDM, surrogate decision maker.

**Table 4 T4:** Schedule for enrollment, interventions, and assessments

	**Study period**							
	**Enrollment**	**Allocation**	**Post-allocation**					**Close-out**
**Time point**	**Day -1**	**0**	**Day 1**	**Day 2**	**Day 3**	**Day 4**	**Day 5**	**Day 30**
**Enrollment**								
Eligibility screen	×							
Deferred or informed consent	×							
Allocation		×						
**Interventions**								
Treatment arm			×/×	×/×	×/×			
Control arm			×/×	×/×	×/×			
**Assessments**								
*Baseline variables*								
Demographics	×							
Past medical history	×							
Type of diagnosis on admission	×							
APACHE-2 score at randomization	×							
SOFA score at randomization	×							
Diagnosis of ARDS at randomization	×							
Time since hemodynamic stability	×							
Length of ICU stay at randomization	×							
*Laboratory results*								
Renal function tests			×	×	×	×	×	
Serum chemistry			×	×	×	×	×	
Serum albumin levels			×	×	×	×	×	
Serum total protein levels			×		×		×	
Colloid osmotic pressure			×		×		×	
Blood gas analysis			×	×	×	×	×	
Troponin I levels			×	×	×	×	×	
Serum lactate levels			×	×	×	×	×	
Complete blood count			×	×	×	×	×	
*Physiologic data*								
Vital signs			×	×	×	×	×	
Glasgow Coma Scale rating			×	×	×	×	×	
Weight			×	×	×	×	×	
Ventilator data			×	×	×	×	×	
Fluid intake and output			×	×	×	×	×	
Diuretic doses and timing			×	×	×	×	×	
*Clinical outcomes*								
Study treatment held?			×	×	×	×	×	
Need for dialysis?			×	×	×	×	×	×
Hypotension requiring fluids			×	×	×	×	×	
Hypotension requiring vasopressors			×	×	×	×	×	
Suspected infection?			×	×	×	×	×	
Intubation status			×	×	×	×	×	×
Date of transfer from ICU			×	×	×	×	×	×
Date of death			×	×	×	×	×	×

APACHE-2, Acute Physiology and Chronic Health Evaluation-2; ARDS, acute respiratory distress syndrome; ICU, intensive care unit; SOFA, Sepsis-related Organ Failure Assessment.

Alternatively, if a treating physician believes that a patient might qualify for the study, and is in urgent need of diuresis, the patient can be considered for deferred consent. To be eligible for deferred consent, patients or surrogate decision makers must have already given consent for administration of blood products. Patients will then be randomized to a study arm and diuretics administered. Study investigators will try to obtain consent from the surrogate decision maker within the next 48 hours. If the surrogate decision maker cannot be located, the patient will be withdrawn from the study. Similarly, if the surrogate decision maker declines participation in the study, the participant will be withdrawn from the study. The deferred consent process is only to be used if the need for diuresis is urgent, and the surrogate decision maker cannot be reached in a timely fashion.

Many strategies have been implemented to aid in recruitment for this pilot study, including the use of recruitment posters and presentations to familiarize ICU staff in participating centers with the study aims and methods. All investigators are either critical care physicians or fellows at the two ICUs where the study is taking place and will aid in recruitment. The inclusive eligibility criteria should also facilitate timely completion of the study.

### Randomization

The randomization process is outlined in Figure 
1. Participants will be randomly assigned to either the control or experimental group in a 1:1 fashion with allocation concealment using an online computer generated randomization schedule. Randomization will be done at the time that the treating physician judges diuresis to be necessary. Allocation of patients to the study group will be carried out by the transfusion medicine service, who will contact a web-based randomization system set up by the statistics team. The transfusion medicine personnel responsible for assignment are distinct from the study personnel enrolling subjects in the study in the ICUs. The transfusion medicine service will keep an electronic list of patient names, study ID numbers, and treatment allocation. Study investigators will not have access to this list and will have to contact the transfusion medicine service to unblind patients for any reason, for example, suspected adverse reaction to a study treatment.

### Blinding

Trial participants, care providers, data collectors, and outcome assessors will be blinded to treatment assignment. Saline placebos will be produced by the hospital’s pharmacy service under sterile conditions by instilling 100 ml of normal saline into evacuated glass bottles identical to those used by the manufacturers of the 25% albumin. The placebos will then be stored in the transfusion medicine department for use in the study. Once a patient has been randomized and assigned to a treatment group, the transfusion medicine service will cover the assigned treatment bottles with an opaque plastic sleeve and dispense them to the ICU, along with opaque intravenous tubing. Fluids will be infused into direct intravenous ports rather than distal intravenous tubing so that all study treatments will be administered directly from the covered bottles and opaque tubing without intervening clear intravenous tubing, which may threaten blinding. The opaque sleeves and intravenous tubing will allow bedside nurses to infuse the fluids without compromising blinding of themselves or the caregiving physicians. To further reduce bias of reporting, the majority of the outcomes of interest in the study are objective (that is, laboratory values, physiologic measurements), rather than subjective outcomes requiring adjudication.

To ensure the safety of study participants, a protocol for emergency unblinding exists. In the event of an adverse reaction that could be attributed to the study treatment (for example, anaphylactic reaction or transfusion-related reaction), the study coordinators will be notified and will unmask group assignment by communicating with the third party personnel in the blood bank responsible for group allocation. Code breaks will occur only under exceptional circumstances. All code breaks (with justification) will be reported on the relevant case report forms.

### Interventions

The treatment and data collection protocol is outlined in Figure 
2. The placebo will be 100 ml of normal (0.9%) saline, administered as an intravenous infusion twice daily. This volume is negligible compared with the total fluid intake of critically ill patients (for feeds, medications, and so on), and unlikely to adversely affect study or patient outcomes, but will still provide adequate blinding of caregivers and study personnel.

**Figure 2 F2:**
[figure not shown]
**Patient treatment and data collection protocol.** IV, intravenous.

The study treatment, either 100 ml of 25% albumin or 100 ml of saline placebo, will be administered as an infusion over 60 minutes, within 2 hours of the patient’s prescribed dose of furosemide. Clinicians will be encouraged to prescribe furosemide twice daily so as to facilitate the timely administration of study treatment prior to furosemide administration.

In the event of new or worsening acute kidney injury, hypotension requiring further boluses of intravenous fluids or vasopressor agents, or if the caregiving team decides that further diuresis is unnecessary, study treatment will be held as long as the caregiving team also holds the furosemide. If a patient’s serum albumin level remains greater than 35 g/l for two measurements greater than 24 hours apart, study treatment will likewise be held. Patients will be monitored for up to 72 hours from randomization and those patients who the caregiving team decide need further diuresis, and have serum albumin levels <35 g/l, will resume the study treatment to which they were assigned.

If the participant develops a suspected adverse reaction to either the albumin, placebo, or furosemide, or the patient leaves the ICU (is transferred to the ward, another institution, or dies) study treatment will be discontinued.

No further administration of colloid intravenous fluids (albumin or starch) will be permitted while the patient is receiving study treatment. In the event that blood product transfusion is required for low serum hemoglobin levels (as opposed to active bleeding with hemodynamic instability), one dose of the study treatment may be held and the prescribed furosemide may be given after the blood transfusion is completed, at the discretion of the caregiving team.

Nursing staff will be provided with a bedside schedule to ensure that the study drug is administered in a timely fashion and that necessary measurements are performed and blood samples collected. The short duration of treatment and the ease of study drug administration will facilitate adherence across both ICUs.

The secondary clinical outcomes that we will collect data for include: (1) duration of mechanical ventilation, measured from time of randomization until extubation that is successful for 24 hours or more, recorded in days; (2) number of episodes of interrupting treatment with furosemide (for example, hypotensive episodes, renal failure, contraction alkalosis); (3) proportion of patients receiving dialysis; (4) length of ICU stay from randomization; (5) ICU mortality; and (6) 30 day mortality. We hypothesize that the addition of 25% albumin will lead to fewer interruptions of diuresis, a reduced incidence of acute kidney injury, and a shorter stay in the ICU.

The secondary physiologic outcomes that we will collect data for include: (1) changes in oxygenation (FiO_2_, PaO_2_/FiO_2_ ratio, oxygenation index) from baseline at day 3 and day 5; (2) changes in dynamic lung compliance, reflecting changes in extravascular lung water, at day 3 and day 5; (3) changes in total fluid balance and body weight, and amount of urine output from baseline at day 3 and day 5; (4) total dose of furosemide used, to assess whether study treatment improves the physiologic response to furosemide; (5) changes in serum albumin and colloid osmotic pressure between treatment groups from baseline at day 3 and day 5, to ensure that the experimental treatment results in the expected increases in these measurements; (6) changes in electrolyte levels (potassium level less than 2.5 mEq/l, sodium level >150 mEq/l), as a way to ensure that no major, potentially harmful changes in serum electrolytes occur as a result of study treatment.

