**Clinical outcomes**				
*Primary outcome*				
Duration of mechanical ventilation	Increased number of ventilator-free days in treatment group	Number of ventilator-free days	Duration of ventilation at time of randomization	*t* test, linear regression
*Secondary outcomes*				
Duration of mechanical ventilation	Decreased duration of mechanical ventilation in treatment group	Duration of mechanical ventilation (days)	Duration of ventilation at time of randomization	*t* test, linear regression
Episodes interrupting treatment with furosemide	Fewer episodes of interruption in treatment group	Number of episodes	None	*t* test
Need for dialysis	Smaller proportion of patients requiring dialysis in treatment group during ICU stay	Proportion of patients requiring dialysis during 30 days	None	Chi-squared or Fisher’s exact statistic
Length of ICU stay	Shorter length of stay in treatment group	Duration of ICU stay	Duration of ICU stay at time of randomization	*t* test, linear regression
ICU mortality	Decreased ICU mortality in treatment group during ICU stay	All-cause mortality (binary)	APACHE-2 and SOFA scores at randomization	Kaplan-Meyer survival curve (time to death)
30-day mortality	Decreased 30-day mortality in treatment group	All-cause mortality (binary)	APACHE-2 and SOFA scores at randomization	Kaplan-Meyer survival curve (time to death)
*Physiologic outcomes*				
Change in oxygenation	Greater increase PaO_2_/FiO_2_ ratio in treatment group at day 3 and day 5	Change in PaO_2_/FiO_2_ ratio	None	*t* test
	Greater decrease in oxygenation index in treatment group at day 3 and day 5	Change in oxygenation index	None	*t* test
Change in lung compliance	Greater increase in dynamic compliance in treatment group at day 3 and day 5	Change in dynamic compliance during study treatment (ml/cmH_2_O)	None	*t* test
Change in fluid balance	Greater net decrease in fluid balance in treatment group at day 3 and day 5	Change in net fluid balance (ml)	Net fluid balance at time of randomization	*t* test, linear regression
Change in body weight	Greater decrease in body weight in treatment group at day 3 and day 5	Change in body weight (kg)	Baseline weight	*t* test, linear regression
Urine output	Greater net urine output in treatment group at day 3 and day 5	Urine output during 3 days of study treatment (ml)	Net fluid balance at time of randomization	*t* test, linear regression

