### Data collection

Data to be collected are listed in Table 
4. Demographic information, prior medical conditions, and reason for admission to ICU will be recorded. The Acute Physiology and Chronic Health Evaluation (APACHE), and Sepsis-related Organ Failure Assessment (SOFA) will be used at the time of ICU admission, the time of randomization, and the treatment end. The administration and doses of intravenous fluids, blood products, and diuretics will also be recorded. Data related to rationale for diuresis will also be collected (peripheral edema, pulmonary edema on chest X-ray, low urine output, elevated central venous pressures or left atrial pressures). Study outcome data collected daily will include vital signs and hemodynamics (if central venous monitoring or pulmonary artery catheters are in place), fluid balance, hourly urine output, weight, ventilator settings (if patient is ventilated), intubation status (including reasons for intubation or re-intubation), oxygenation parameters (SaO_2_, FiO_2_, PaO_2_/FiO_2_ ratio, oxygenation index). Blood samples, to determine standard and extended electrolyte levels, renal profile, complete blood count with differential, serum albumin and total protein levels, and blood gas data, are routinely collected in patients undergoing diuresis and will be collected at least daily. Colloid osmotic pressure and serum total protein will also be assessed at baseline, day 3 and day 5. Study data will be collected from the time of ICU admission to hospital discharge or 30 days after enrollment. All of these data are measured routinely in the ICU and subject to minimal interobserver variation. Colloid osmotic pressure will be measured using the Wescor model 4220, which has a precision of ± 0.03 mmHg
[21].

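### Ventilation duration and ICU stay have no rule for death, and ICU mortality is called binary but given a Kaplan-Meier method

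*Protocol article*

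**What the plan says.** - **Ventilation duration.** The Outcomes section defines it as "measured from time of randomization until extubation that is successful for 24 hours or more, recorded in days". Table 2 gives the hypothesis "Decreased duration of mechanical ventilation in treatment group" and the method as t test and linear regression.
- **ICU stay.** The Outcomes section has "length of ICU stay from randomization". Table 2 has "Shorter length of stay in treatment group", with the same methods.
- **Death rule.** Outcomes and Statistical methods give one for ventilator-free days only: death within 28 days scores 0.
- **ICU mortality.** Table 2 states "Decreased ICU mortality in treatment group during ICU stay", labels the measure binary, lists APACHE-2 and SOFA as covariates, and names the method as "Kaplan-Meyer survival curve (time to death" (closing bracket omitted here). The 30-day mortality row has the same measure, covariates and method.
- **Population.** None of the five inclusion criteria under Participants requires mechanical ventilation. Statistical methods puts all randomized participants in the main analysis.
- **Use.** Statistical methods says the pilot makes no clinical analysis and that these analyses are pre-specified for the definitive trial, which will absorb the pilot data. Dissemination policy allows by-arm results from the pilot only if it proves non-feasible.

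**The concern.** A patient who dies on the ventilator never reaches successful extubation. An analyst following the text must either end the duration at death or leave the patient out. Both choices can shorten the mean in the arm with more deaths, and Table 2 reads shorter as benefit. ICU stay has the same gap.

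For a patient not ventilated at randomization, duration has no defined value, yet all randomized patients are to be analysed.

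In the ICU-mortality row, outcome type and method do not match. Death in the ICU is a yes/no result once the stay is over. A time-to-death curve needs a rule for patients who leave alive, and none is given. If discharge is treated as censoring, the curve estimates mortality as though discharged patients still faced the ICU death hazard.

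At stake is the reading of three secondary outcomes in the definitive trial. A harmful effect on survival could appear as faster recovery, and a real difference in ICU deaths could be missed.

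**Working it through.** The documents give no expected value for any of these outcomes. The only sample-size figures concern feasibility (for example 1.96² × 0.925 × 0.075 / 0.075² = 47.4, against 47 stated) and do not bear on this point. All hazards below are assumptions, taken as constant per day.

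**1. Ventilation duration.** Extubation hazard e = 0.10 in both arms; death hazard d = 0.02 v 0.04; follow-up 30 days; λ = e + d = 0.12 v 0.14.

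- Death ends the duration: mean = (1 − exp(−30λ))/λ.
  - (1 − exp(−3.6))/0.12 = 8.1 days
  - (1 − exp(−4.2))/0.14 = 7.0 days
- Deaths on the ventilator: (d/λ)(1 − exp(−30λ)).
  - (0.02/0.12) × 0.973 = 16%
  - (0.04/0.14) × 0.985 = 28%
- Deaths dropped, only patients extubated by day 30 kept: mean = 1/λ − 30·exp(−30λ)/(1 − exp(−30λ)).
  - 8.33 − 0.84 = 7.5 days
  - 7.14 − 0.46 = 6.7 days
- Ventilator-free days, no death after extubation assumed: e × [28/λ − (1 − exp(−28λ))/λ²].
  - 0.10 × (233.3 − 67.0) = 16.6 days
  - 0.10 × (200.0 − 50.0) = 15.0 days

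Treatment has no effect on extubation here, and one arm has twice the death hazard. Both versions of duration favour that arm. Ventilator-free days, which have a death rule, go the right way.

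Across extubation hazards of 0.10 and 0.15 and death hazards of 0.01 v 0.02, 0.01 v 0.03 and 0.02 v 0.04, simulated mean duration was 0.3 to 1.2 days shorter in the arm with more deaths. Ventilator-free days were 0.9 to 1.8 lower.

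**2. ICU stay.** Put ICU discharge alive in place of extubation. The same formulas apply, so the same hazards give 8.1 v 7.0 days.

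**3. ICU mortality at 30 days.** Death hazard a, discharge hazard b. With discharge censored, 1 − KM = 1 − exp(−30a). The proportion who die in the ICU is a/(a+b) × (1 − exp(−30(a+b))).

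| a | b | 1 − KM | Die in ICU |
|---|---|---|---|
| 0.01 | 0.08 | 25.9% | 10.4% |
| 0.01 | 0.15 | 25.9% | 6.2% |
| 0.02 | 0.10 | 45.1% | 16.2% |
| 0.02 | 0.15 | 45.1% | 11.7% |
| 0.03 | 0.10 | 59.3% | 22.6% |

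The third and fourth rows show the missed difference: faster discharge lowers ICU deaths from 16.2% to 11.7%, and the censored curve reads 45.1% in both.

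**The case against.** The other side has several good points.

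- **Censoring at ICU discharge is not documented.** If discharged patients stay in the risk set to day 30 with no ICU-death event, the curve recovers the true proportion and the gap in step 3 disappears. The Abstract's data collection until ICU discharge hints at censoring, but Data collection runs to hospital discharge or 30 days, and Table 4 records transfer and death dates at day 30. The Kaplan-Meier bias is therefore conditional. The mismatch between a binary outcome and a time-to-death method is not.
- **Adjustment is not lost.** A reader might infer that APACHE-2 and SOFA can never enter, since a Kaplan-Meier curve takes no covariates. The sensitivity rows of Table 2 provide multivariable regression with the listed covariates for all outcomes.
- **Unventilated patients do not fix ventilator-free days.** A reader might infer that they score near 28 whatever the treatment and inflate the sample by a known factor. Deaths score 0, later intubation lowers the score, the model already carries prior ventilation duration as a covariate, and no ventilated share is given. Nor does "ventilator settings (if patient is ventilated" prove unventilated enrolment, since it also fits patients extubated during follow-up. The inclusion criteria are the firmer evidence.
- **Death is not ignored overall.** The planned primary outcome scores it as worst, and two mortality outcomes stand beside the durations, so a harmful shortening would be partly exposed.
- **Such rules are often left to an analysis plan.** That is true of a missing rule. Here the protocol itself fixes the extubation endpoint, the t test and the Kaplan-Meier method.

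**Conclusion.** The point stands in limited form. As written, both duration outcomes can favour the arm with more deaths. Under the assumed hazards the false gain is 0.3 to 1.2 days; the direction follows from the definitions, and the size depends on the hazards. Ventilation duration is undefined for patients not ventilated at randomization. The ICU-mortality row is internally mismatched, and if discharge alive is censored it overstates ICU mortality (45% v 16% in the example) and can hide a real difference.

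The documents do not support a claim that Kaplan-Meier necessarily misstates ICU mortality here, nor any figure for dilution of ventilator-free days. Kaplan-Meier for 30-day mortality is sound provided vital status is known to day 30. These are secondary outcomes for a later trial, and the pilot's feasibility conclusion is untouched. The change should be made before the definitive analyses are settled, or before any by-arm pilot results are published.

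**What to change.** Revise the affected rows of Table 2:

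- **ICU mortality:** compare proportions by chi-squared or Fisher's exact test, as Table 2 already does for dialysis, with logistic regression on APACHE-2 and SOFA as the adjusted analysis.
- **30-day mortality:** keep Kaplan-Meier, and state that vital status is sought to day 30 for everyone, including patients discharged earlier.
- **Ventilation duration:** restrict to patients ventilated at randomization and report the cumulative incidence of extubation alive, with death as a competing event.
- **ICU stay:** report the cumulative incidence of ICU discharge alive in all randomized patients, with death as a competing event.
- **Ventilator-free days (optional):** also report the result in patients ventilated at randomization.

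The cost is small. Intubation status, ICU transfer date and date of death are already scheduled through day 30 in Table 4. The Abstract and Data collection sections, which give different ends of data collection, should be aligned with that schedule. Cumulative incidence is less familiar to readers than mean days, and the restricted ventilation analysis uses fewer patients.
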